### Outcome measures

#### Primary outcome measure

The primary outcome measure is the Olerud and Molander Ankle Score (OMAS) [26] reported at 12 weeks following surgery. The OMAS is a validated ankle-fracture PROM [27, 28] consisting of nine Likert-styled questions; three symptom- and six function-focussed questions. It is scored 0–100; poorest to best, respectively, and has been treated as a continuous scale in the Cochrane ankle fracture review [13] and has been recommended by both Cochrane reviewers [13] and NICE [23].

#### Secondary outcome measures

Secondary outcomes including the OMAS collected at 2 and 6 weeks post surgery, as baseline and end-of-intervention measures, respectively and at 24 and 52 weeks post surgery, as medium- and long-term follow-ups. Other secondary outcomes include: the Ankle-Fracture Outcome of Rehabilitation Measure (A-FORM) [29] and the EQ-5D-5 L [30] PROMs, which are collected at the same time points as the OMAS. Other function-focussed outcomes include the Physical Activity Record Scale (PARS) [31], the Clinical Physical Activity Questionnaire (CPAQ) [32], the use of walking aids, return to work and return to driving. X-ray findings and adverse events are also recorded.

When answering Likert-styled questions within the PROMs, if a participant is unsure which Likert option to select, they are advised to select the poorer outcome. This approach is particularly pertinent at the 2-week and 6-week time points, when answering function-related questions such as walking, as post-operative clinical instructions would have been to remain non-weight-bearing. This is not an anticipated concern for the primary outcome, being at 12 weeks, nor the subsequent follow-ups.

Objective measures are included at the 2-week and 6-week time points: non-weight-bearing dorsiflexion and plantar flexion ROM and, ankle (figure-of-8) and calf (circumference) measures. Participants will be invited to attend for repeated outcome assessments at 12 weeks, 24 weeks and 52 weeks, with the additions of weight-bearing dorsiflexion, walking speed, balance and isokinetic plantar-flexion strength. Those declining will be encouraged to complete and return the appropriate PROMs questionnaires.

### Participant timeline

Recruitment and consent may take place from the in-patient stay until and including the 2-week post-surgery outpatient review. Only after all baseline outcome measures are recorded, does randomisation take place, see Figs. 1 and 2.

**Fig. 1 Fig1:**
[figure not shown]
Standard Protocol Items: Recommendations for Interventional Trials (SPIRIT) Figure of enrolment, interventions and assessments. Key: *EMADE* early motion and directed exercise, *PROMs* Patient-reported outcome measures. *Study PROMs: Olerud Molander Ankle Score (OMAS), Ankle-Fracture Outcome of Rehabilitation Measure (A-FORM), EQ-5D-5 L, work and leisure activities, walking aid use and return to driving. **Option for patients to attend for Laboratory-based objective measures

**Fig. 2 Fig2:**
[figure not shown]
A schematic diagram of the patient’s journey through the early motion and directed exercises (EMADE) ankle study. Key: *EMADE* early motion and directed exercise, *PROMs* patient-reported outcome measures

The data collection time points (post surgery) are: baseline at 2 weeks, end of intervention at 6 weeks, and at three research follow-up time points; 12 weeks and 24 weeks as short- and mid-term follow-ups, respectively, and at 52 weeks as a long-term follow-up and the trial end point. For participant’s convenience, the 2-week and 6-week EMADE sessions are combined with the orthopaedic 2-week and 6-week reviews. The 12-week, 24-week and 52-week PROMs data may be collected via either return post (postage pre-paid), electronically or in person according to participant choice. Participants undergoing objective assessment will attend the David Greenfield Human Physiology Unit, Medical School, University of Nottingham, UK.

### Allocation and Blinding

An online computer service, www.sealedenvelope.com is used for randomisation. This facility generated the codes concealed from the research team, on a 1:1 allocation basis to either group, with random order of permuted blocks (sizes of 4, 6 and 8). Over the duration of the trial, there is greater potential that those with syndesmosis screw(s) may require further surgery. To mitigate against risk of allocation imbalance, stratification of this sub-group will be designed into the randomisation.

### Blinding (masking)

It is not possible to blind the participant nor the therapist from the treatment allocation.

However, to reduce risk of bias, 12-, 24- and 52-week paper PROMs are completed by participants, concealed from the researchers and stored in sealed opaque envelopes. A third party, blinded to the intervention group inputs the data. The electronic PROMs are web-based, held by Bristol Online Survey (BOS), www.onlinesurveys.ac.uk. Via this system at the appropriate time points, participants are e-mailed a single-use link to their e-PROM.

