### Data processing

PROM data collection is paper based, with participant number 55 onwards being offered the option of completing PROMs online. Once paper-based 12-week, 24-week and 52-week PROMs are completed the participant seals them in a windowless opaque envelop and returns them to the researchers (postage pre-paid). These are securely stored and subsequently opened in batches by an individual blinded to group allocation, who inputs the data into a holding database for subsequent transfer into SPSS for reporting and statistical analysis. For audit purpose, after inputting each batch, a ‘read-only’ copy is stored in a separate protected folder. A separate copy is used for data screening and cleaning, guided by good practice [33] and may include self-evident corrections [34] where appropriate. While filters and error alerts will reduce inputting errors, 20% of entries will be cross-checked against the paper PROMs for discrepancies. Data changes will be recorded for blinded adjudication. For audit purposes a copy of the cleaned and checked data will also be saved as a ‘read-only’ copy and stored separately. The design of the e-PROMs does not permit questions to be left unanswered, mitigating against problems of incomplete data and once the participant completes their PROM the original dataset is locked against further alterations. The system permits data transfer into SPSS.

The research team and statistician will conduct the analysis. The statistician will conduct the primary outcome analysis independently and is blinded to group allocation. Data and reason for any patient excluded prior to randomisation will be reported, but not carried into the main analysis. Descriptive statistics will be produced, within and between each intervention group(s) for demographics and outcomes at all data time points. Continuous data will be summarised as mean and standard deviation and confidence intervals (CI) (95% CI and *p* value threshold ≤ 0.05) for the PROM outcome data. Median and interquartile ranges will be used where appropriate statistical assumptions are not met, whereas categorical data will be presented as frequencies and proportions and analysed using either chi-square or Fisher’s exact test as indicated (*p* value of ≤ 0.05). Non-parametric tests will be employed where appropriate. Analysis will be conducted on the intention-to-treat (ITT) basis.

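### PROM concealment and blinded entry are specified only for weeks 12, 24 and 52, so week 6 is the one post-randomisation PROM time point with no stated safeguard

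*Protocol article*

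**What the plan says.** **Where concealment applies.** The Blinding (masking) section states that "to reduce risk of bias, 12-, 24- and 52-week paper PROMs are completed by participants, concealed from the researchers". The forms are then kept in sealed envelopes, and a third party blinded to group enters the data. Data processing repeats the list: "Once paper-based 12-week, 24-week and 52-week PROMs are completed the participant seals them in a windowless opaque envelop". The same section has a blinded individual open the envelopes in batches and enter the contents.

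**What is collected at week 6.** Secondary outcome measures has "Secondary outcomes including the OMAS collected at 2 and 6 weeks post surgery, as baseline and end-of-intervention measures, respectively". A-FORM and EQ-5D-5L are "PROMs, which are collected at the same time points as the OMAS", so they too fall at week 6. Participant timeline places randomisation after all baseline measures, so the week-2 forms come before allocation and the week-6 forms after it.

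**How the week-6 visit is arranged.** The text with Fig. 2 says that "the 2-week and 6-week EMADE sessions are combined with the orthopaedic 2-week and 6-week reviews". It offers postal, electronic or in-person return for weeks 12, 24 and 52 and gives no route for week 6.

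**Advice on answering.** Secondary outcome measures says that "if a participant is unsure which Likert option to select, they are advised to select the poorer outcome", and singles out weeks 2 and 6 as the time points where this matters most.

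**The article's own assessment.** The Discussion says that the design limits bias where it can, PROM collection and processing included. It concedes unblinded recording for the objective outcomes only.

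**The concern.** A safeguard described twice with the same three time points is a stated scope, not just an omitted detail. Week 6 is the only PROM time point after randomisation that falls outside it.

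It is also the time point where the safeguard would be most useful. Participants and therapist know the allocation. EMADE participants have had weekly face-to-face sessions, and their last one shares the day with the clinic review. The article also expects uncertainty about the function questions at that visit.

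At stake are the end-of-intervention comparison of OMAS, A-FORM and EQ-5D-5L, any analysis over the whole study period that includes week 6, and the week-6 EQ-5D-5L value that would feed the QALY. The primary outcome, OMAS at week 12, lies inside the concealed set.

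**Working it through.** **1. PROM time points set side by side**

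| Week | Relative to randomisation | Sealing and blinded entry stated | Visit shared with an EMADE session |
|---|---|---|---|
| 2 | before | no | yes, but forms precede allocation |
| 6 | after | no | yes |
| 12 (primary) | after | yes | no |
| 24 | after | yes | no |
| 52 | after | yes | no |

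Week 6 is the only row that is both after randomisation and without a stated safeguard.

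**2. Weight of week 6 in the QALY**

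The article does not fix the QALY method, so trapezoidal interpolation is assumed. Each time point's weight is half the interval before it plus half the interval after it:

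- week 2: 4/2 = 2
- week 6: (4 + 6)/2 = 5
- week 12: (6 + 12)/2 = 9
- week 24: (12 + 28)/2 = 20
- week 52: 28/2 = 14

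The total is 50 weeks. Week 6 carries 5/50 = 10% of the area, or 5/52 = 0.096 of a year.

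**3. What a reporting shift would do to the QALY**

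The documents give no size for such a shift, so a range is assumed. Spurious QALY difference = shift × 5/52. The cost is the article's own £54 to £75 for EMADE (Discussion), divided by that spurious difference and with no true effect.

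| Assumed between-arm shift in week-6 utility | Spurious QALY | Apparent cost per QALY |
|---|---|---|
| 0.02 | 0.0019 | about £28,100 to £39,000 |
| 0.05 | 0.0048 | about £11,200 to £15,600 |
| 0.10 | 0.0096 | about £5,600 to £7,800 |

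The extra cost is small, so a QALY difference of a few thousandths can move the ratio a long way.

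**4. Week-6 OMAS**

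The plan's sample size reproduces first: 2 × (1.96 + 0.84)² × 19.5² / 10² rounds up to 60 per arm, or 120 in total, as stated. With 60 per arm, and assuming that the SD of 19.5 also holds at week 6, the standard error of the difference is 19.5 × √(2/60) = 3.56. An assumed between-arm reporting bias of 2, 3 or 5 points would raise the two-sided 5% error to about 9%, 13% or 29%.

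Steps 3 and 4 show sensitivity only. They do not show that any shift exists.

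**The case against.** The other side has substantial points.

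- **Completion in clinic is not stated.** A reader might infer that the week-6 forms are known to be filled in unprotected at the shared visit. The text does not say so. The return options listed for the later weeks make clinic completion likely. However, e-PROM links go out at time points the article does not list, and online completion was offered from participant 55, so week 6 is not excluded. The figures are not shown, and a fuller protocol may hold more. This stands. What survives is that the article confines the safeguard to three named weeks, twice, and then describes PROM bias control without qualification.
- **Sealing is not blinding.** A reader might infer that week 6 alone is exposed to biased reporting and that envelopes would cure it. Participants know their allocation throughout, and forms may be returned in person later too. Envelopes limit what staff can see or influence and leave self-report bias in place. This stands.
- **The 'poorer option' advice is not arm-specific.** A reader might infer that it distorts the treatment difference, or that prompting acts in the EMADE arm alone. The advice covers any unsure participant, and everyone is kept non-weight-bearing up to week 6. A shift common to both arms cancels from the difference, and nothing in the article shows unequal use. This stands.
- **The size is assumed.** No utility shift or true QALY gain can be taken from the documents, so a claimed percentage error in the QALY result would be unsupported. This stands.
- **Reach is limited.** The PROM objectives name weeks 12, 24 and 52, and secondary analyses are described as hypothesis-generating. This bears on priority but does not remove the gap.

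**Conclusion.** The point holds in a limited form. The article specifies PROM concealment and blinded entry for weeks 12, 24 and 52 only. That leaves week 6 as the single post-randomisation PROM time point with no stated safeguard, at a visit combined with the EMADE session. The Discussion's general statement on PROM bias does not acknowledge this.

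The reach is the secondary end-of-intervention OMAS, A-FORM and EQ-5D-5L and, under trapezoidal interpolation, about 10% of the week 2 to 52 QALY area. The week-12 primary analysis is untouched. The documents do not establish that bias has occurred, its direction, or its size. The case for acting is that the means of closing the gap are already in use at the other time points.

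**What to change.** - **Procedure.** In Blinding (masking) and Data processing, add week 6 for remaining participants: self-completion before contact with the therapist or researcher at that visit, by sealed opaque envelope or e-PROM, with entry by the same blinded third party.
- **Advice.** Keep the 'if unsure' advice unchanged for all PROMs and print it identically on the forms for both arms. Dropping it for EQ-5D-5L alone is not advised. With 111 participants already joined, that would change how a repeated measure is administered partway through the trial.
- **Reporting.** Record the date of the change. In the Discussion, qualify the statement on PROM bias for week-6 data already collected.
- **Sensitivity analysis.** Report QALYs with and without week-6 EQ-5D-5L. Without it, the trapezoid weights for weeks 2, 12, 24 and 52 become 10/2 = 5, (10 + 12)/2 = 11, 20 and 14, still 50 weeks in total. A difference between the two results would not by itself prove bias, because a real early benefit would also show at week 6.

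**Cost.** The envelopes, the online system and the blinded data-entry person already exist, so this is a change of procedure. The downside is that earlier participants' week-6 data stay unconcealed. Against the target of 156, 156 − 111 = 45 participants were still to join at submission (33 against the 144 in the abstract), so the procedural change reaches a minority. The reporting and sensitivity steps cover everyone.

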## Sample size, data processing and statistical methods

### Sample size calculations

It was estimated that a total of 120 participants will be required based on a minimal clinical important difference of 10 points on the OMAS, with a standard deviation of 19.5, significance level of 5% and powered at 80%. Allowance for attrition was set initially at 20% but, due to higher-than-expected dropout rates, this was increased to 30%, yielding a target of 156 to enter the study at randomisation.

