**Method/design:**

We have designed a pragmatic randomised controlled trial (p-RCT) to compare the EMADE intervention against usual care. We will recruit 144 independently living adult participants, absent of tissue-healing comorbidities, who have undergone surgical stabilisation of isolated Weber B ankle fractures. The EMADE intervention consists of a non-weight-bearing progressive home exercise programme, complemented with manual therapy and education. Usual care consists of immobilisation in a non-weight-bearing below-knee cast. The intervention period is between week 2 and week 6 post surgery. The primary outcome is the Olerud and Molander Ankle Score (OMAS) patient-reported outcome measure (PROM) at 12 weeks post surgery. Secondary PROMs include the EQ-5D-5 L questionnaire, return to work and return to driving, with objective outcomes including ankle range of motion. Analysis will be on an intention-to-treat basis. An economic evaluation will be included.

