### Trial design and study setting

This is a prospective, pragmatic randomised controlled trial (p-RCT) of superiority design, with participants allocated in a 1:1 ratio to either of two parallel groups. The trial is based in the fracture clinic of the Queen’s Medical Centre, Nottingham University Hospitals, Nottingham, UK, with other sites being considered.

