To test the primary outcome measure hypothesis that the EMADE physiotherapy intervention, as described will perform better than usual care, the difference in group means of the primary outcome, OMAS values at 12 weeks post surgery, will be statistically compared. This will be through applying an independent *t* test with significance taken as *p* value of ≤ 0.05 and the inclusion of confidence intervals (CI at 95% CI and *p* value of ≤ 0.05 threshold). Where data is not found to be normally distributed such that parametric tests cannot be utilised, the non-parametric Mann-Whitney *U* test will be employed (*p* value ≤ 0.05).

There is a lack of consensus in the academic literature on how to handle missing data [35, 36]. However, based on the 120 sample size, the following sequential approach will be applied for the primary outcome:If missing data is 5% or less, conduct analysis based on complete-case analysisIf missing data is greater than 5% and up to 10%:Conduct analysis based on pairwise deletion (assuming missing at random (MAR)) and thenConduct multiple imputation analysisIf these two analyses yield comparable results, then it will be assumed that the missing data has not influenced the outcome of the trialIf the two analyses yield notable differences, to accommodate for the missing data, sensitivity analysis will be conducted based on the statistician’s adviceIf missing data exceeds 10%, detailed discussions will be held with the study statistician

Interpretation of secondary outcome and sub-group analysis will require caution due to risks of type II errors and, because of where post hoc analysis may demonstrate association, causation may not be supported. Secondary analyses will be performed for hypothesis generation. The difference in group mean scores for the secondary outcomes; EQ-5D-5 L and A-FORM at 12 weeks post surgery will be analysed in a similar manner to the primary outcome. The one-way analysis of covariance (ANCOVA), including follow-up time as a covariance, will be applied to assess these outcomes across the complete study period.

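### The 30% attrition allowance is applied as 120 × 1.3 rather than 120 / 0.7, so the target of 156 leaves about 109 evaluable and about 76% power; the abstract still gives 144

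*Protocol article*

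**What the plan says.** Under Sample size calculations, the protocol article states: "It was estimated that a total of 120 participants will be required". The basis is a "minimal clinical important difference of 10 points on the OMAS", "with a standard deviation of 19.5, significance level of 5% and powered at 80" per cent. The same paragraph says the attrition allowance began at 20% and that, "due to higher-than-expected dropout rates, this was increased to 30%, yielding a target of 156 to enter the study at randomisation".

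The abstract (Method/design) gives another number: "We will recruit 144 independently living adult participants".

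Two other places bear on the calculation. Trial design and study setting has "participants allocated in a 1:1 ratio to either of two parallel groups". Data processing fixes the primary comparison of 12-week OMAS: "This will be through applying an independent *t* test with significance taken as *p* value of ≤ 0.05".

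**The concern.** An attrition rate is a fraction of those randomised. To end with a required number N after losing a fraction d, one randomises N / (1 − d). Multiplying N by (1 + d) always gives too few, and the shortfall grows with d. Both published targets, 144 and 156, fit the multiplied form exactly and neither fits the divided form.

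The trial raised its allowance because dropout was running above expectation, so the allowance has to work at the new rate. If it does not, the power at the trial's own planning assumption is below the 80% that readers will take 156 to protect.

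The abstract and the sample-size section also disagree about the target. The Trial status section reports 111 participants at submission, below both figures, so the number at which recruitment ends still mattered.

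**Working it through.** **Inputs**

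- Difference 10 OMAS points, SD 19.5, significance 5%, power 80% (Sample size calculations).
- 1:1 allocation (Trial design and study setting).
- Independent t test on 12-week OMAS (Data processing).
- Attrition 20% initially, 30% as revised (Sample size calculations).
- Sidedness is not stated with the calculation. I assume two-sided because it reproduces the plan's 120; a one-sided test gives 48 per arm, 96 in total.

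**Step 1: reproduce the 120**

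n per arm = 2 × (SD / difference)² × (z₀.₉₇₅ + z₀.₈₀)² = 2 × (19.5 / 10)² × (1.960 + 0.842)² = 59.7, so 60 per arm and **120 in total**. This matches the plan. The exact t-test calculation gives 60.7, so 61 per arm and 122 in total, which is close enough that I raise no point on it.

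**Step 2: the attrition step**

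| Attrition allowance | N × (1 + d) | N / (1 − d) | Figure in the article |
|---|---|---|---|
| 20% | 120 × 1.20 = 144 | 120 / 0.80 = 150 | 144 (abstract) |
| 30% | 120 × 1.30 = 156 | 120 / 0.70 = 171.4, so 172 | 156 (sample-size section) |

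The stated target is 172 − 156 = 16 below what 30% attrition requires.

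**Step 3: what the targets deliver**

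Evaluable = randomised × (1 − d). Power is for a 10-point difference with SD 19.5, two-sided 5%.

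| Randomised | Attrition | Evaluable | Power, normal approximation | Power, t test |
|---|---|---|---|---|
| 156 | 30% | 109.2 | 76.4% | 75.7% |
| 156 | 23.1% | 120 | 80.2% | 79.6% |
| 156 | 20% | 124.8 | 81.7% | 81.1% |
| 172 | 30% | 120.4 | 80.3% | 79.7% |
| 144 | 20% | 115.2 | 78.6% | 77.9% |
| 144 | 30% | 100.8 | 73.1% | 72.2% |

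For the first row by the normal approximation: 109.2 / 2 = 54.6 per arm; standard error = 19.5 × √(2 / 54.6) = 3.73; 10 / 3.73 = 2.68; 2.68 − 1.96 = 0.72; Φ(0.72) = 0.764.

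**Step 4: break-even attrition**

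1 − 120 / 156 = 36 / 156 = 23.1%. Up to that rate, 156 does keep 120.

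**Step 5: detectable difference at 80% power**

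By the t test it rises from 10.06 points with 120 evaluable to 10.55 with 109; by the normal approximation, from 9.97 to 10.46. The increase is about half a point either way.

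**The case against.** The best defence has five parts.

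**A 30% allowance can mean adding 30%.** Read that way, 156 is correct arithmetic, and the 80% power is formally attached to 120 rather than to 156. But the text ties the allowance to dropout rates. An add-on of 30% covers 23.1% dropout, and a reader would still conclude that 30% loss is covered. The label changes and the shortfall stays.

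**The 30% has no time point.** The primary outcome is at 12 weeks and follow-up runs to 52 weeks. If 30% describes loss over the whole trial, loss at 12 weeks could be under 23% and 156 would suffice. This stands as a condition on the size of the effect: the 76% applies if 30% lack the 12-week OMAS. However, the allowance is attached to the primary-outcome calculation, and the article offers no other rate for 12 weeks.

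**The effect is modest.** This is fair. It is about four power points, and none up to 23.1% attrition. Type I error and the treatment comparison are unaffected.

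**A reader can tell which target is in force.** Largely true: the sample-size section narrates the change from 20% to 30%, so 144 is recognisable as a leftover. For the same reason the row pairing 144 with 30% loss is illustrative only, since the plan nowhere combines them. The abstract is still current text and still wrong. Reading 144 as recruited and 156 as randomised does not help, because under Participant timeline consent precedes randomisation, so recruits cannot be fewer than those randomised.

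**Imputation could recover the loss.** The missing-data rules under Data processing specify multiple imputation only for more than 5% and up to 10% missing. Above 10% they defer to discussion with the statistician, so nothing fixed in the plan restores power at 30%.

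**Conclusion.** The concern holds. The requirement of 120 is sound. The target of 156 does not follow from it at 30% attrition; the matching figure is 172. If 30% of those randomised lack the 12-week OMAS, 156 leaves about 109 evaluable, with about 76% power for 10 points in place of 80%. The abstract's 144 contradicts the target in force and carries the same error at the superseded 20% rate.

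This rests on a two-sided 5% test, on the 30% applying to the primary outcome at 12 weeks, and on equal loss in the two arms. The consequence is moderate, but the article states a wrong figure that the trial relies on, and it should be corrected.

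**What to change.** 1. In Sample size calculations, keep 156 and restate what it delivers: 120 evaluable, and so 80% power, if attrition at 12 weeks is at most 23%; about 109 evaluable and about 76% power for a 10-point difference if attrition is 30%. If the sponsor wants to state both 30% attrition and 80% power, the figure to give is 172.
2. In the same sentence, say that the attrition rate refers to the 12-week OMAS and that the test is two-sided.
3. In the abstract, replace 144 with the target in force.

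The cost is wording in two places and a slightly less favourable power statement. Restating the figure needs no extra participants; choosing 172 would add 16 to the randomisation target.
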